## Abstract

**Background:**

Either benznidazole (BZN) or nifurtimox (NFX) is recommended as equivalent to treat *Trypanosoma cruzi* infection. Nonetheless, supportive data from randomised trials is limited to individuals treated with BZN in southern cone countries of Latin America.

**Methods:**

The goal of this randomised, concealed, blind, parallel-group trial is to inform the trypanocidal efficacy and safety of NFX and its equivalence to BZN among individuals with *T. cruzi* positive serology (TC+). Eligible individuals are TC+, 20–65 years old, with no apparent symptoms/signs or uncontrolled risk factors for cardiomyopathy and at negligible risk of re-infection. Consenting individuals (adherent to a 10-day placebo run-in phase) receive a 120-day BID blinded treatment with NFX, BZN or matching placebo (2:2:1 ratio). The four active medication arms include (1) a randomly allocated sequence of 60-day, conventional-dose (60CD) regimes (BZN 300 mg/day or NFX 480 mg/day, ratio 1:1), followed or preceded by a 60-day placebo treatment, or (2) 120-day half-dose (120HD) regimes (BZN 150 mg/day or NFX 240 mg/day, ratio 1:1). The primary efficacy outcome is the proportion of participants testing positive at least once for up to three polymerase chain reaction (PCR) assays (1 + PCR) 12–18 months after randomisation. A composite safety outcome includes moderate to severe adverse reactions, consistent blood marker abnormalities or treatment abandons. The trial outside Colombia (expected to recruit at least 60% of participants) is pragmatic; it may be open-label and not include all treatment groups, but it must adhere to the randomisation and data administration system and guarantee a blinded efficacy outcome evaluation. Our main comparisons include NFX groups with placebo (for superiority), NFX versus BZN groups and 60CD versus 120HD groups (for non-inferiority) and testing for the agent-dose and group-region interactions. Assuming a 1 + PCR ≥ 75% in the placebo group, up to 25% among BZN-treated and an absolute difference of up to ≥ 25% with NFX to claim its trypanocidal effect, 60–80 participants per group (at least 300 from Colombia) are needed to test our hypotheses (80–90% power; one-sided alpha level 1%).

**Discussion:**

The EQUITY trial will inform the trypanocidal effect and equivalence of nitroderivative agents NFX and BZN, particularly outside southern cone countries. Its results may challenge current recommendations and inform choices for these agents.

**Trial registration:**

ClinicalTrials.gov, NCT02369978. Registered on 24 February 2015.

**Electronic supplementary material:**

The online version of this article (10.1186/s13063-019-3423-3) contains supplementary material, which is available to authorized users.

## Background

The World Health Organization (WHO) estimates that 8 million people are infected by *Trypanosoma cruzi*, the parasite causing Chagas disease, and 10,000 of these people are expected to die every year [1]. Different health authorities recommend either nifurtimox (NFX) or benznidazole (BZN) as treatment for *T. cruzi*-infected individuals [2–5]. The purpose of using these trypanocidal agents is to reduce the parasitic load (expecting to prevent, delay or reduce the impact of clinical complications) and to reduce its transmission [6]. However, a number of reasons hinder this potential opportunity. Firstly, convincing evidence of efficacy from randomised trials is limited to parasite-related (but not patient-important) outcomes [7], to treatment with BZN (but not NFX) and to individuals from Brazil and Argentina and more recently Bolivia (but not other countries in Latin America) [8–13]. Secondly, the tolerance to this treatment, typically offered for 60–90 days, is still suboptimal, with an abandon rate ranging from10 to 20% reported in these studies.

In the above context, decision-makers, at both the individual and population levels, will benefit from more information on the efficacy and safety of NFX as treatment for *T. cruzi* infection. The trypanocidal effect of NFX, demonstrated in a single trial in Brazil [14], needs replication and validation in other populations. Furthermore, treatment with BZN in the BENEFIT trial proved to be trypanocidal for participants from Argentina and Brazil (80% of the study population) but not for (the remaining 20%, 502 and 78) participants from Colombia and El Salvador [11]. Geographical variability of trypanocidal efficacy of BZN had been previously reported in a large case series of school children from Bolivia, Honduras and Guatemala [15]. This highlights the importance of expanding the existing information on the trypanocidal efficacy of NFX and exploring its equivalence to BZN. This emerging information may be of particular interest for endemic countries with smaller representation in previous trials, such as Colombia.

In the direction of addressing this research gap, this paper describes the methods for Phase 3 of the Cardiovascular Health Investigation and Collaboration from Countries of America to Assess the Markers and Outcomes of Chagas disease (CHICAMOCHA 3) project, the Equivalence of Usual Interventions for Trypanosomiasis (EQUITY) trial.

## Methods

Overall, the aim of the EQUITY trial is to evaluate, among young adults with chronic *T. cruzi* infection but no symptomatic chronic Chagas cardiomyopathy, the trypanocidal effect and safety of a treatment with NFX compared with BZN or placebo.

### Study design

We will conduct a randomised, concealed, multi-centre, parallel-group, blind trial, testing the superiority of NFX over placebo and its non-inferiority compared with BZN.

### Setting and participants

EQUITY will seek collaborating centres from Colombia and other countries in Latin America offering care to outpatients with *T. cruzi* chronic infection. Study centres will be actively seeking eligible candidates with local centres for serology diagnosis, blood banks or health authorities. The eligible population will be individuals aged 20–65 of both sexes, with serology diagnosis (positive results for at least two out of three serological tests including enzyme-linked immunosorbent assay [ELISA] and indirect immunofluorescence of haemagglutination over the last 10 years), negligible risk of re-infection (residence in an urban setting or a suburban/rural area with no history of vector infestation or transmission) and the capability to attend regular follow-up visits at the study centres (Table 1).

**Table 1 Tab1:** Study eligibility criteria

Eligibility	Exclusion criteria
• Men or women 20–65 years of age	• Previous treatment with nifurtimox or benznidazole
• Positive serology for *T. cruzi* (at least two different techniques applied to the same blood sample) in the last 10 years	• Lack of compliance/tolerance to a 10-day run-in period
• No clinical suspicion, or active risk factors for, chronic cardiomyopathy	• Abnormal values in blood cell counts or laboratory tests for hepatic and renal function
• Negligible risk of vector *T. cruzi* re-infection	• Any medical/social condition hindering free participation
• Capable of complying with the planned study visits	• Current or planned pregnancy, or not using secure birth methods for women of childbearing age

Exclusion criteria include the following: previous treatment with BZN or NFX or participation in trials testing trypanocidal drug candidates; any symptom suggesting chronic Chagas (or other forms) of cardiomyopathy or uncontrolled risk factors for it; persistent abnormalities in liver/kidney blood function tests (alanine amino transferase [ALAT]/aspartate amino transferase [ASAT] twofold normal values or creatinine over 1.2 mg/dl observed at least twice); women of childbearing age who have positive pregnancy tests or are unwilling to use secure birth control methods; or any concomitant health problem judged by the study physician as potentially interfering with free participation, health or well-being during the study or administration of treatment.

### Interventions

The randomly allocated study interventions may differ for centres across countries. While in Colombia EQUITY will offer masked (i.e. similar-looking) treatments, including placebo or active treatments, in the remaining centres it will be a pragmatic, open-label trial, where the control group may not receive medication (see further explanation in the following paragraphs).

In Colombian centres, before randomisation, in order to ensure adherence to study interventions, eligible, consenting individuals will go over a 10-day, run-in treatment (with placebo). This treatment placebo, blinded for participants, has a similar appearance to the study drug and will be given in similar fashion (2 capsules twice a day [BID]). Those reporting tolerance and adherence (not experiencing symptoms judged as moderate/severe and taking at least 80% of the capsules) will be prescribed a blinded treatment of 2 capsules BID for 120 days. This includes a sequence-concealed, randomly allocated treatment with any of the following five treatment groups (ratio 1:1:1:1:1):NFX 480 mg/day for 60 daysNFX 240 mg/day for 120 daysBZN 300 mg/day for 60 daysBZN 150 mg/day for 120 daysPlacebo

Two of the four groups with active treatment will have a 60-day, conventional dose (60CD) of either NFX or BZN, whereas the other two groups include 120-day, half-dose (120HD) treatment. As the prescribed study treatment for all groups takes 120 days, the 60CD groups will receive another 60-day masked placebo treatment that precedes or follows the active treatment in a randomly assigned sequence. Figure 1 summarises the study arms and assigned treatments. To ensure the blinding to participants and their relatives, treating physicians and study teams, the study medication will be packaged in a similar fashion. We used similar gelatin capsules to include and mask the contents of the original tablets of active treatments or placebo (a mix of microcrystalline cellulose and magnesium stearate), as shown in Fig. 2. The study medication was packed in bottles of 120 capsules (intended to last for 2 months) labelled with the study name and treatment codes, making the study arms indistinguishable from each other.

**Fig. 1 Fig1:**
[figure not shown]
Process of treatment allocation

Outside Colombia, because of (1) resource constraints to organise a centralised shipment of study medication or to mask locally their study medication, or (2) local interpretation of the evidence, clinical practice patterns and/or regulations on using trypanocidal treatments, the protocol may have variations in the interventions. EQUITY investigators at those centres will have flexibility to decide on (1) which of the proposed active treatment groups to include and (2) whether or not to have a control group receiving no treatment. Groups receiving active treatment may be any two or all four treatment groups described above. If two groups are chosen, they must use either different agents given at the same dose level and treatment length (either 60CD or 120HD) or the same agent (either NFX or BZN) given at different dose levels and treatment lengths. The choice of including a group not receiving active treatment will depend on the judgement of local investigators or regulatory agencies on whether it is necessary (1) to prove a trypanocidal effect of NFX or (2) to start trypanocidal treatment right upon serology diagnosis.

For centres outside Colombia choosing to include a group receiving no treatment, the allocation ratio will be the same for each active treatment group (i.e. 1:1:1 for those having two active treatment groups and 1:1:1:1:1 for those including all four active treatment groups). In all circumstances, however, all EQUITY centres will use a computerised central randomisation system with a concealed sequence to allocate the local choice of study treatments. All study sites will also have to comply with a blinded process for outcome assessment.

### Comparisons

EQUITY will test two main efficacy hypotheses, driving the primary comparisons. Firstly, we will test the superiority of NFX, comparing a composite of groups receiving this medication against those allocated to placebo/no treatment (trypanocidal effect of NFX). Secondly, we will test the non-inferiority of (1) a composite of NFX groups compared with those including BZN and (2) 60CD regime groups of any active medication compared with those receiving 120HD regimes. The above comparisons place BZN/60CD as standard treatment, assuming its superiority to placebo. Under this hypothesis, for NFX/120HD to be a valid alternative, we will require its trypanocidal efficacy to be at least two thirds of that for BZN/60CD (see the statistical assumptions made in the “Sample size calculations” section).

Centres outside Colombia may provide data for some, but not all, planned comparisons, depending on their choice of treatment groups. For example, data from centres including only active treatment groups with both NFX and BZN will contribute to test the hypothesis of non-inferiority of NFX to BZN but not to evaluate the trypanocidal efficacy itself. Whatever the choice of treatment groups, however, under our study design our primary comparisons may vary in the number of participants included, but they will only be between randomly allocated treatment groups at a centre level.

We will also test the dose-agent and the treatment-region (southern/northern) interactions for the above comparisons. Data from countries outside Colombia will be included in the applicable comparisons, depending on their treatment groups. We plan to conduct separate sensitivity analyses for our primary comparisons including all randomised participants and those included in Colombia. The safety evaluation will follow the same comparisons described for efficacy.

Secondary comparisons are intended only for efficacy of BZN. They will include (1) testing its superiority over placebo, testing for the treatment-region interaction, and (2) testing the non-inferiority of BZN 120HD compared with BZN 60CD in the overall population. As for the primary comparisons, data from centres outside Colombia may be included, provided they have chosen to randomise their participants to each of these groups.

A subgroup, exploratory analysis will include (1) age strata at inclusion (20–44/45–65 years), (2) presence/absence of electrocardiographic abnormalities and (3) region of origin (southern/northern South America) for all the planned efficacy comparisons.

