### Sample size calculations

The planned hypotheses in this study will be based on the following assumptions for its sample size:The proportion of participants in the placebo group with at least one positive PCR out of three tests (1 + PCR, the primary outcome for efficacy) will be 75% or higher.As a standard of trypanocidal efficacy, the proportion of (1 + PCR) in the group receiving conventional treatment with BZN (based on results of the BENEFIT trial) will be up to 30% (or 25% in a group receiving BZN in a regime with better tolerance).A treatment with NFX, to be considered non-inferior to BZN, should have at least two thirds of its trypanocidal effect, which is, in terms of the above assumptions, 45% of 1 + PCR (or up to 50% in a group receiving a regime with lower tolerance/efficacy).

Based on the above assumptions, having at least 60–80 participants per study group will allow enough (at least 80%) power to identify a true difference between NFX and placebo or BZN (as negative or positive control for superiority or non-inferiority, respectively), testing a one-tailed hypothesis at an alpha level of 1%. Colombian centres should account for at least 60% of the study population, or 300 participants in the study (60 participants for each group). The overall goal of recruitment, including participants for centres outside Colombia, will be 500, as long as they include at least 80 participants allocated to every study arm (which may vary, depending on the treatment groups chosen at centres outside Colombia). Table 3 shows the scenarios for power calculations for the comparisons on efficacy.

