### Statistical analysis

Reporting of trial results will include a description of the enrolment process and the most relevant characteristics of the participants. For this purpose we will use counts and proportions or means and standard deviations for discrete and continuous variables, respectively.

Our outcome measures will be discrete variables, with the exemption of mean changes in the BNP levels, a secondary outcome for efficacy. For the purpose of evaluating the efficacy of NFX over placebo, we will test a hypothesis of no difference in the proportions of 1 + PCR at an alpha level of 1%. For the purpose of testing the equivalence of NFX to BZN or between 60CD and 120HD regimes, we will run a one-tailed non-inferiority test at an alpha level of 1%. In order to test for agent-dose interaction for the above comparisons, we will construct logistic regression models with the primary outcome as the event, and the comparison groups and study arms (e.g. NFX 60CD or NFX 120HD) as predictor variables. We will include the interaction dose*agent term in the model and run this test for no differences at an alpha level of 5%.

For the purpose of evaluating mean changes of BNP among groups, we will test for differences using independent-sample Student’s *t* tests comparing the groups of interest (alpha level of 1%). For the dose-agent interaction test (alpha level 5%), we will run an analysis of covariance with the mean changes as response, the comparison and study arms as factors and the interaction term.

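### NFX is tested against a BZN pool of which about half receives 120HD, while the two-thirds rule and its 45% limit come from conventional-dose BZN, and no rule links the two

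*Protocol article*

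**What the plan says.** The Comparisons section sets the agent test as "a composite of NFX groups compared with those including BZN", so both BZN regimens form the comparator. It then says: "The above comparisons place BZN/60CD as standard treatment, assuming its superiority to placebo". For an alternative to be acceptable, "we will require its trypanocidal efficacy to be at least two thirds of that for BZN/60CD".

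The Sample size calculations section takes its 30% positive-PCR rate from the outcome "in the group receiving conventional treatment with BZN" and turns two thirds of that effect into a 45% limit for NFX. The placebo rate "will be 75% or higher".

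The Interventions section allocates Colombian participants equally to five arms. Two-arm centres elsewhere may compare "different agents given at the same dose level and treatment length (either 60CD or 120HD"), or one agent across the two regimens.

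The checks bearing on the half dose are a primary 60CD versus 120HD comparison over both agents, a secondary comparison "testing the non-inferiority of BZN 120HD compared with BZN 60CD in the overall population", and a dose-by-agent term in a logistic model, where the authors will "run this test for no differences at an alpha level of 5" per cent. The article does not say what any of these results does to the NFX conclusion.

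**The concern.** The rule refers to one regimen of BZN and the test uses two. If 120HD is weaker, the BZN pool moves towards the untreated rate, and the pooled difference between agents may shrink for reasons unrelated to how NFX performs at conventional dose.

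The trial is meant to inform whether NFX can be recommended as an equivalent of BZN as now used. A pooled result could be reported as non-inferiority to standard BZN although NFX 60CD keeps less than two thirds of the BZN 60CD effect. The comparator, the anchor and the limit are all stated in the article, so the mismatch lies in the article's own text.

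**Working it through.** **Inputs.** From the article: placebo 75%; conventional BZN 30%; NFX limit 45%; one-sided alpha 1%; 60 per arm in Colombia and at least 80 per arm overall; 500 participants in total, 300 of them from Colombia; 5% losses. That leaves 57 or 76 evaluable per arm. Assumed, because the article gives no figure: the effect kept at 120HD, and a fixed margin of 45 − 30 = 15 points in the analysis.

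**The plan's own figures.** Conventional BZN effect: 75 − 30 = 45 points. Two thirds is 30 points, so the limit is 75 − 30 = 45%, as stated. The range of 60–80 per group is reproduced for 75% versus 50% at one-sided 1% with 5% losses. Placebo against two pooled NFX arms needs 60 per arm at 80% power and 76 at 90%. A 1:1 comparison needs 78 at 80%. The cells of Table 3 are not available, so only the range in the text could be checked.

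**Share of 120HD in the BZN pool.**
- Colombia: 60/120 = 50%.
- Overall: of the 200 participants outside Colombia, 100 bring all five arms from 60 to 80. If the other 100 come from NFX/BZN centres using 60CD only, BZN is 130 + 80 and the share is 80/210 = 38%. If they come from 120HD-only centres, it is 130/210 = 62%.

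**Largest NFX 60CD deficit that the pool admits.** Let f be the 120HD share and k the fraction of effect that each agent keeps at 120HD. The pooled difference is d × [(1 − f) + f·k], where d is the 60CD difference. Setting it to 0.15 gives d = 0.15 / [(1 − f) + f·k]; the share of the BZN 60CD effect kept is (0.45 − d)/0.45. With f = 0.5:
- k = 1: d = 0.15, NFX 60CD 45%, 67% kept.
- k = 0.5: d = 0.20, NFX 60CD 50%, 56% kept.
- k = 0: d = 0.30, NFX 60CD 60%, 33% kept.

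At f = 0.38 the last two become 59% and 46% kept.

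**False non-inferiority with NFX 60CD truly at 45%.** Probability = Φ[(0.15 − D)/SE − 2.326], where D is the true pooled difference and SE² is the sum of p(1 − p)/(4n) over the four active arms.
- k = 0.5: BZN 30% and 52.5%, NFX 45% and 60%, D = 0.1125. SE is 0.064 (n = 57) or 0.056 (n = 76), giving 4% or 5%.
- k = 0: BZN 30% and 75%, NFX 45% and 75%, D = 0.075. SE is 0.060 or 0.052, giving 14% or 19%.

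The interaction test (two-sided 5%, log-odds scale) has 10–11% power in the first case and 20–25% in the second.

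**BZN losing more than NFX.** Hold NFX at 45% in both regimens, with a 50:50 pool.

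| BZN 120HD | Pool | Limit, 15-point margin | Effect kept | Effect kept, ratio rule on pool | Claim probability, 15-point margin | Interaction power |
|---|---|---|---|---|---|---|
| 40% | 35% | 50% | 56% | 59% | 6–8% | 13–15% |
| 50% | 40% | 55% | 44% | 52% | 22–29% | 34–44% |
| 60% | 45% | 60% | 33% | 44% | 50–64% | 63–75% |

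The two effect-kept columns apply to NFX sitting exactly at the limit in question.

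**Cases where nothing loosens.**
- Ratio rule, proportional loss: the factor (1 − f) + f·k multiplies both pooled effects and cancels. At k = 0.5 and at k = 0, pooled NFX effect / pooled BZN effect stays 30/45 = 0.667.
- Equal loss in percentage points, balanced arms: the pooled difference stays 15 points and the error stays 1%.
- 120HD better than 60CD, for example BZN 25%: pool 27.5%, limit 42.5%, 72% kept. The rule tightens.

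**The case against.** The strongest reply is that the article states the rule as a ratio. It gives 45% only as what two thirds amounts to under its planning rates, and the Statistical analysis section fixes no numerical margin. On that reading, proportional loss does no harm. This stands, and the figures under proportional loss must be read with that condition. It does not cover BZN losing more than NFX, where a ratio rule on the pool also loosens relative to BZN 60CD.

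A second reply is that BZN/60CD may denote factor levels: BZN is the standard for the agent test and 60CD for the regimen test. That is possible, and pooled BZN would then be intended. The planning rate nevertheless comes from conventional BZN, so the text needs reconciling either way.

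Third, a weak half dose would usually show. With a 15-point margin, the primary regimen test would declare 120HD non-inferior with probability about 0.2% at k = 0.5 and practically never at k = 0. This stands too, and low interaction power is therefore not the main worry when both agents weaken together. What is missing is the consequence of that finding for the NFX statement. An analysis plan that is not shown may order the claims, but it would still inherit the mismatch in the article.

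A reader might infer that at least half of the comparator is always 120HD. The Interventions section does not support this, because centres may run 60CD only and the share can fall to about 38%. A reader might also cite 160/220 = 73%, with all 200 outside participants in 120HD arms. That leaves the BZN 60CD arm at 60 and breaks the condition of 80 per arm.

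**Conclusion.** The concern holds in conditional form. The comparator tested is not the regimen to which the rule is anchored, and the article does not say how a poor 120HD result limits the NFX conclusion. The consequence is material if the analysis uses a fixed 15-point margin and 120HD keeps only part of each agent's effect, or if BZN loses more than NFX at half dose. The inflated error rates further assume equal regimen shares and a normal approximation.

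The documents do not support the stronger inference that pooling always favours NFX: the direction depends on the form of the margin and on how 120HD performs, and neither is known. Nor do they support saying that the plan has no safeguard. Relevant tests are planned, but none is tied to the claim.

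**What to change.** Keep the pooled NFX versus BZN test as primary. In the Comparisons section, reconcile the pooled comparator with the BZN/60CD anchor, and state whether the margin is a fixed difference or a retained fraction. Word the pooled conclusion as applying to the mix of regimens studied. Always report NFX minus BZN, with its interval, within 60CD and within 120HD. When 120HD is not shown non-inferior to 60CD, rest any statement about conventional-dose BZN on the 60CD stratum.

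The cost is a few sentences and two interval estimates. The downside is precision. With both agents at 30% and a 15-point margin, power = Φ[0.15/√(2 × 0.3 × 0.7/n) − 2.326]. The 60CD-only comparison (n = 57 or 76 per group) has 28–38% power, against 56–70% for the pooled test (n = 114 or 152), so the statement about conventional-dose BZN may stay inconclusive.

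A strict gate, with no pooled claim at all unless 120HD passes first, is not recommended. Even with equal regimens (BZN 30% and NFX 45% at both), 120HD would pass only about 52–66% of the time. Limiting the wording gives most of the protection and leaves the primary test intact.

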## Discussion

Closing gaps in clinical research is critical for a field like Chagas disease, where major initiatives focused over the last decades on vector control to interrupt transmission [18, 19]. Most with relatively little data, particularly trials on trypanocidal treatment, have originated in Brazil and Argentina. More recently, there have been trials originating outside Latin America (e.g. in Spain and Canada). In the landscape of research on trypanocidal therapy, the EQUITY trial will tackle an important question on therapy for *T. cruzi* infection. As both NFX and BZN are currently used under recommendations and distribution of health authorities, this may be seen as a phase IV study. However, by expanding and validating the information on the effects of NFX, the study has the potential to challenge current recommendations on using alternatively NFX or BZN as similar interventions. In particular, this trial may benefit its target population from countries with fewer or no data from previous trials, or those where the best evidence indicates that BZN lacks a trypanocidal effect. Colombia, the country originating this trial, fits this situation. EQUITY thus represents a step forward for Colombia in terms of conducting this investigator-initiated, publicly funded trial for this largely neglected disease [20].

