EQUITY has some limitations. Firstly, its primary efficacy outcome is parasite-related. Establishing an effective regime that is well tolerated is an intermediate, necessary step for future testing of its clinical impact. In fact, in the placebo-controlled BENEFIT trial (where 20% of the population did not respond to BZN and 13% abandoned their treatment), the clinical impact went consistently towards benefit, but without statistically significant effect (7% reduction in its primary outcome, a composite of cardiac complications or death) [11]. Thus, choice of a treatment scheme with a better efficacy/tolerance ratio would be critical to identify a potential clinical impact. Secondly, as the trial relies on limited resources, it will have a limited geographical variety in its population. By having Colombia as the main participating country, we will address two needs: to run a new trial testing NFX (the first in Colombia, where a previous quasi-experiment showed positive results [26]), and to replicate (or challenge) previous results of the BENEFIT trial showing no trypanocidal effect. Thirdly, our study will test a limited amount of possibilities for trypanocidal therapy. The EQUITY trial will focus on the foundations to use NFX and to recommend it as an equivalent of BZN. Keeping the trial within this reach allows statistical power for the two main questions, at a cost of leaving, for example, combinations, other treatment schemes and other agents untested.

Finally, conducting a trial like EQUITY will, for the local capacity, provide a useful and constructive experience. This trial will increase much-needed clinical trial data on *T. cruzi*-infected populations from Andean countries. In that regard, EQUITY will join two recent trials including Bolivian patients or immigrants living in Spain [12, 13]. Investigator-initiated trials originating from Colombia are still scarce, and are a challenge for promotion among funding and regulatory agencies as well as research departments and laboratories. For this and other neglected tropical diseases, this type of trials may also be seen as a responsibility for endemic countries.

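### Non-inferiority to BZN assumes that BZN beats placebo, which the protocol itself doubts for Colombia, and no superiority result is made a condition for the claim

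*Protocol article*

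**What the plan says.** Comparisons names BZN at the conventional regimen as the reference: "The above comparisons place BZN/60CD as standard treatment, assuming its superiority to placebo". The next sentence says that, under this hypothesis, the alternative must reach at least two thirds of the reference's efficacy. NFX versus placebo or no treatment is the first primary comparison. Non-inferiority of NFX to BZN, and the comparison of the 60CD and 120HD regimens, come second. BZN versus placebo appears later: "Secondary comparisons are intended only for efficacy of BZN". Centres without a control group may contribute to the NFX-BZN comparison.

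Sample size calculations puts placebo at 75% or more positive PCR and BZN at up to 30% (or 25%), citing the earlier placebo-controlled BZN trial. It puts the NFX limit at 45% (or up to 50%).

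On that same earlier trial, Background says BZN was trypanocidal in Argentina and Brazil "but not for (the remaining 20%, 502 and 78) participants from Colombia and El Salvador". The Discussion speaks of countries with little trial data, or "those where the best evidence indicates that BZN lacks a trypanocidal effect. Colombia, the country originating this trial, fits this situation". It also gives as an aim to "replicate (or challenge) previous results of the BENEFIT trial showing no trypanocidal effect". On the make-up of the sample: "Colombian centres should account for at least 60% of the study population, or 300 participants in the study".

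Statistical analysis gives the non-inferiority test as one-tailed at 1%. It states no margin, no test statistic and no condition.

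**The concern.** A non-inferiority result shows that the new treatment works only if the reference works in the population studied. Here the reference effect is assumed to be 45 to 50 points, while the protocol says the best evidence is that this effect is absent in the country supplying most participants. If BZN does little there, two inactive treatments will look alike and a margin of 15 to 25 points is easily met. The Discussion presents the trial as the basis for recommending NFX as an equivalent of BZN, so a non-inferiority statement that does not depend on BZN working could be read as evidence of efficacy. The regimen comparison has the same structure, and Comparisons lists no test of pooled 60CD or pooled 120HD against control.

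**Working it through.** **Inputs.** From the protocol: one-sided alpha 1% (z = 2.326); 1:1:1:1:1 allocation in Colombia with 60 per arm, so 120 NFX, 120 BZN and 60 placebo; 5% losses, leaving 114, 114 and 57; the rates given above. Assumed here: the all-arms-equal case, the mixed case, an equal split of 500 participants, and a fixed-margin reading of the test.

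**The plan's own figure (60 to 80 per group, at least 80% power).**
- Superiority, 75% v 50%, pooled variance under the null: 74 per group, and 74/0.95 gives 78.
- Non-inferiority, n = (2.326 + 0.842)² × 2p(1−p)/m². With p = 25% and m = 25 points: 61, or 65 after losses. With p = 30% and m = 25 points: 68, or 72 after losses.
- With p = 30% and m = 15 points: 188, or 198 after losses, per comparison group.

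So 60 to 80 is reproduced for a 25-point difference or margin. The cells of Table 3 are not in the text available and could not be checked.

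**Implied margins.** 45 − 30 = 15 points keeps 30 of 45 points, which is two thirds. 50 − 25 = 25 points keeps 25 of 50, which is half. These are the ends of the range.

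**Neither drug works (all arms 75%).** P(declare) = Φ(m/SE − 2.326), with SE = √(2 × 0.75 × 0.25/114) = 0.0574.
- m = 0.15: 2.615 − 2.326 = 0.289, giving 61%.
- m = 0.25: 4.359 − 2.326 = 2.033, giving 98%.
- With 200 per agent (500 split equally): 87% and over 99.9%. A larger trial makes it worse.

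**Would the placebo comparison expose it?** In simulation with 114/114/57, non-inferiority is declared while NFX fails against placebo in 60.6% (15 points) and 97.1% (25 points) of all trials. That is 0.606/0.613 = 99% and 0.971/0.979 = 99% of the false declarations.

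**With the condition that NFX and BZN each beat control (one-sided 1%).**

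| True rates NFX/BZN/control | Margin | No condition | Both beat control |
|---|---|---|---|
| 75/75/75 | 15 | 61% | 0.1% |
| 75/75/75 | 25 | 98% | 0.2% |
| 30/30/75 (planning) | 15 | 56% | 56% |
| 30/30/75 (planning) | 25 | 96% | 96% |
| 57/57/75 (mixed) | 15 | 48% | 17% |
| 57/57/75 (mixed) | 25 | 94% | 35% |

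**Mixed case.** Assume no effect in Colombia (60%) and the planning effect elsewhere (40%): 0.6 × 75 + 0.4 × 30 = 57%, an effect of 18 points. A 15-point margin then keeps 3 of 18 points (17%), and a 25-point margin exceeds the whole effect. Two-thirds retention would allow 6 points.

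**Retention test as an alternative.** Contrast: p(NFX) − ⅔p(BZN) − ⅓p(control). Variance: pN(1−pN)/nN + (4/9)pB(1−pB)/nB + (1/9)pC(1−pC)/nC.
- All arms equal: the contrast is zero, so the error is 1%.
- 30/30/75: contrast −0.15, SE 0.055, power 66% with 60 per arm and 79% with 80 per arm. The fixed 15-point margin gives 56% and 70%.
- 25/25/75: contrast −0.167, SE 0.052, power 80% with 60 per arm. The fixed 25-point margin gives 98%.

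**The case against.** **The fixed margin is inferred.** Comparisons words the criterion as a fraction of effect, conditional on the superiority hypothesis. The 45% and 50% figures stand in the sample-size section as planning conversions, and Statistical analysis gives no margin. A reader might infer that the written test uses fixed points and ignores the placebo arm. The text does not say so, and a retention test would hold the error at about 1%. This stands as a limit on the 61% to 98%. Still, the only numerical version of the criterion is in fixed rates, and centres that cannot estimate a placebo effect may feed the test. The fixed-margin reading is therefore plausible and has to be settled in writing.

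**A null would be seen.** A reader might infer that two inactive drugs could pass unnoticed. They would not: NFX versus placebo is primary, BZN versus placebo is secondary, and region interactions and a Colombia-only sensitivity analysis are planned. This stands, and it limits the harm. None of these results, however, has a stated consequence for the non-inferiority claim.

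**A condition on BZN alone would be incomplete.** If NFX works and BZN does not, losing the non-inferiority claim must not hide the NFX effect. This stands, and the fix provides for it.

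**Test order is often left to the analysis plan.** A separate plan may add a condition. The protocol, however, itself writes down the assumption and the evidence against it.

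**Conclusion.** The point holds as a missing condition on a primary claim. The protocol assumes a BZN effect that it elsewhere says the best evidence denies for at least 60% of its sample, and it makes no superiority result a prerequisite for non-inferiority. On a fixed-margin reading with all arms at 75%, the claim is made in about 61% to 98% of trials of the Colombian size. That range depends on the margin reading and on the all-equal scenario. The same arithmetic applies to pooled 60CD versus 120HD.

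The documents do not support saying that the non-inferiority test must be replaced by a retention contrast at no cost. The contrast gains power against a 15-point margin but loses it against the 25-point margin (80% v 98% with BZN at 25%). With BZN at 30% it stays below the stated 80% at both 60 and 80 per arm. It is a trade-off, suited to a supportive role.

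**What to change.** State the following before unblinding.

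- Non-inferiority or equivalence of NFX to BZN is claimed only if NFX and BZN each beat placebo or no treatment at one-sided 1%, in centres with a randomised control group. Report the result for Colombia as well.
- If NFX beats control and BZN does not, report superiority of NFX over control and the NFX-BZN difference, and make no equivalence claim.
- Apply the same condition to the regimen comparison: pooled 60CD and pooled 120HD must each beat control.
- State the margin or test form explicitly.
- As a supportive analysis, report the retained fraction of effect against the concurrent control.

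**Cost.** Wording and comparisons on data already collected; no extra participants. At the planning rates the power cost is negligible. The real cost is that the claim is lost when the reference shows no effect, and often when its effect is diluted: in the assumed mixed case the chance of claiming falls from 48% to 17% (15 points) or from 94% to 35% (25 points).
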